## Abstract

**Background:**

Patients with human papillomavirus-positive (HPV+) oropharyngeal squamous cell carcinoma (OPC) have substantially better treatment response and overall survival (OS) than patients with HPV-negative disease. Treatment options for HPV+ OPC can involve either a primary radiotherapy (RT) approach (± concomitant chemotherapy) or a primary surgical approach (± adjuvant radiation) with transoral surgery (TOS). These two treatment paradigms have different spectrums of toxicity. The goals of this study are to assess the OS of two de-escalation approaches (primary radiotherapy and primary TOS) compared to historical control, and to compare survival, toxicity and quality of life (QOL) profiles between the two approaches.

**Methods:**

This is a multicenter phase II study randomizing one hundred and forty patients with T1–2 N0–2 HPV+ OPC in a 1:1 ratio between de-escalated primary radiotherapy (60 Gy) ± concomitant chemotherapy and TOS ± de-escalated adjuvant radiotherapy (50–60 Gy based on risk factors). Patients will be stratified based on smoking status (< 10 vs. ≥ 10 pack-years). The primary endpoint is OS of each arm compared to historical control; we hypothesize that a 2-year OS of 85% or greater will be achieved. Secondary endpoints include progression free survival, QOL and toxicity.

**Discussion:**

This study will provide an assessment of two de-escalation approaches to the treatment of HPV+ OPC on oncologic outcomes, QOL and toxicity. Results will inform the design of future definitive phase III trials.

**Trial Registration:**

Clinicaltrials.gov identifier: NCT03210103. Date of registration: July 6, 2017, Current version: 1.3 on March 15, 2019.

## Background

Oropharyngeal squamous cell carcinoma (OPC) is rapidly increasing in incidence, associated with rising rates of human papillomavirus (HPV) infection [1, 2]. Patients with HPV-positive (HPV+) OPC have substantially better treatment response and overall survival (OS) than patients with HPV-negative (HPV-) disease [3]. Historically the management of OPC has relied on radiotherapy (RT) based approaches as older surgical techniques required large incisions and mandibulotomies with high surgical morbidity and mortality [4]. The addition of concurrent chemotherapy to radiation improved oncological outcomes [5]. However, acute and long term side effects of RT or chemoradiation (CRT) can be severe, including frequent swallowing dysfunction, mucositis, xerostomia, fibrosis, osteoradionecrosis, neutropenia, neurotoxicity and hearing loss [6].

The introduction of minimally invasive transoral surgical techniques including transoral robotic surgery (TORS) and transoral laser microsurgery (TLM) has led to a revival of surgery as the primary treatment of OPC [7, 8]. While primary surgery with transoral surgery (TOS) can avoid some of the side effects of radiotherapy, it can have rare serious consequences such as fatal hemorrhage, stroke, shoulder dysfunction and dysphagia [9].

Currently, there is no level I evidence to favor one treatment strategy over the other. Instead, treatment selection is largely driven by institutional and patient biases with the majority of patients in the United States receiving surgery (82% of T1-T2 disease) [7], while most patients receive primary RT in Canada and Europe [10, 11].

The ORATOR trial is the only trial to examine the question of a primary RT vs. primary TOS approach in a randomized fashion [12]. This phase II trial included 68 patients with OPC regardless of HPV status, and randomized patients to RT (70 Gy, with chemotherapy if N1–2) or TOS plus neck dissection (with or without adjuvant RT/CRT, based on pathology). The primary endpoint was swallowing-related quality of life (QOL) at 1 year, measured using the MD Anderson Dysphagia Inventory (MDADI) [13]. The study found that at 1 year there was a statistically significant difference in swallowing QOL but that this difference did not represent a clinically meaningful change (less than a 10-point difference).

Since the ORATOR trial opened in 2012, the landscape has further shifted to recognize the clinical importance of HPV status. The impact of HPV on outcomes has been so substantial that a separate staging system has been created to better represent the prognosis of these patients [3, 14]. Although not yet part of routine clinical care, research is now focused on de-intensification of treatment in HPV+ OPC, in an attempt to reduce adverse events while maintaining excellent oncologic outcomes. Patients with HPV-related OPC have an excellent chance of survival, and therefore may have to deal with the sequelae of therapy for many decades [3]. With excellent rates of cure, post-treatment QOL becomes of paramount importance. Trials focusing on both primary RT and primary surgical approaches have de-escalated radiotherapy doses; two key trials that are currently underway include NRG-HN-002 and ECOG-3311 [15, 16].

NRG-HN-002 [15] included 308 patients in a phase II parallel-arm design investigating de-intensification in a low-risk p16+ population (T1–2 N1-N2b or T3 N0-N2b as per AJCC 7th edition, and ≤ 10 pack-year smoking history). Arm 1 was conventionally fractionated CRT with 60 Gy (2 Gy/fraction) given in 6 weeks with weekly cisplatin 40 mg/m^2^ and Arm 2 was accelerated RT alone with 60 Gy (2 Gy/fraction) given in 5 weeks with 6 fractions per week. The trial had co-primary endpoints with progression-free survival (PFS) and QOL at 2 years with acceptability criterion of PFS of ≥85% and an MDADI score ≥ 60. Early results presented in abstract format showed the CRT arm met the acceptability criteria for both PFS and MDADI, while the accelerated radiotherapy arm did not meet the PFS acceptability criterion [15].

ECOG-3311 focuses on a primary surgical approach for cT1–2 N1–2b (as per AJCC 7th edition) HPV+ OPC patients, de-escalating the adjuvant RT dose for intermediate risk patients based on surgical pathology. After resection, if a patient has any of: close margins, < 1 mm of extranodal extension (ENE), 2–4 lymph nodes (LN) involved, perineural invasion (PNI) or lymphovascular invasion (LVI) they are randomized in a 1:1 ratio to standard dose adjuvant RT (60 Gy) or de-escalated adjuvant RT (50 Gy). The primary endpoint for this trial is PFS. This trial has completed accrual, but results are not yet reported [16].

Given the dramatic rise in the incidence of HPV disease and the paucity of high-quality data comparing treatment options, the management of HPV+ OPC is arguably the most contentious issue in head and neck oncology [17, 18]. The purpose of this randomized trial is to assess the safety of two de-escalation approaches (primary RT and primary surgery) in early T stage HPV+ OPC by comparing to historical control, and to compare survival, toxicity and QOL profiles between the two approaches. The primary radiotherapy approach is based on the chemoradiation arm of HN002, and the primary surgery approach is based on the treatment paradigm of ECOG-3311 [15, 16].

## Methods/design

The objectives of this trial are to:
Compare OS relative to historical controls for de-intensified primary radiotherapy [60 Gy ± chemotherapy] versus TOS and neck dissection [± adjuvant 50 Gy radiotherapy] in patients with early T-stage HPV+ squamous cell carcinoma of the oropharynx.Compare PFS, toxicity and QOL profiles.

Our hypothesis is that for patients with HPV+ T1–2N0–2 (as per AJCC 8th edition) OPC, de-intensified primary RT and primary surgery with de-intensified adjuvant therapy will achieve 2-year OS rates of 85% or greater.

### Study design

This study is an open-label phase II multi-centre randomized trial, and is designed to assess two potential treatment de-escalation approaches, comparing each to a historical control, with the potential goal of evaluating one or both compared to standard CRT in a subsequent phase III trial. The required sample size is 140 patients. Participating centres will be tertiary, academic hospitals or radiotherapy treatment centres in Canada (updated list of participating centres available on clinicaltrials.gov: identifier NCT03210103). Patients will be randomized between a primary RT-based approach (Arm 1) vs. a primary surgical approach (Arm 2) in a 1:1 ratio using a permutated block design (Fig. 1). There will be one stratification factor: smoking status (< 10 vs. ≥ 10 pack-years). Arm 1 of this trial is based on the chemoradiation arm of HN002 (60 Gy ± concomitant weekly cisplatin based on clinical nodal disease) [15], and Arm 2 is similar to the treatment paradigm of ECOG-3311 (TOS ± adjuvant RT (50–60 Gy) based on risk factors) [16].

**Fig. 1 Fig1:**
[figure not shown]
Study Schema

### Primary endpoint

OS
◦ Defined as time from randomization to death from any cause

This study was originally launched with a primary endpoint of PFS. The results of the original ORATOR trial became available in February 2019. These suggested that OS would be a preferred endpoint for ORATOR2 as both arms in ORATOR showed excellent OS in p16+ cancers (both > 92% at 2 years). OS is preferred as the primary endpoint to evaluate de-escalation, since it was evident in ORATOR that progression events, whether local, regional, or distant, can often be salvaged for cure with surgery, radiation, or systemic therapy including immunotherapy. Therefore, in Feb 2019, without knowledge of outcomes data from ORATOR2, this trial was amended to promote OS from a secondary to primary endpoint, and demote PFS to a secondary endpoint.

### Secondary endpoints

2-year PFS (comparison with historical controls)
◦ Time from randomization to disease progression at any site or death PFS events are defined as death from any cause, or first recurrence of tumor at any site (including local, regional, or distant). Second primary tumors (e.g. head and neck cancer at a different site, such as laryngeal cancer) will not be included as PFS events.2-year OS and PFS comparisons between Arm 1 and Arm 2Swallowing-related QOL at 1-year post-treatment
◦ Assessed using the MDADIQOL at other time points
◦ Assessed using the MDADI, the European Organisation for Research and Treatment of Cancer (EORTC) Quality of Life Cancer Patients general (QLQ-C30) and head & neck (H&N35) scales, the Voice Handicap Index (VHI-10), the Neck Dissection Impairment Index (NDII), the Patient Neurotoxicity Questionnaire (PNQ), and the EuroQOL 5-Dimension 5-Level (EQ-5D-5 L).Toxicity
◦ Assessed by the National Cancer Institute Common Toxicity Criteria (NCI-CTC) version 4Other functional measurements, including, measured by:
◦ Feeding tube rate at 1-year◦ Common Toxicity Criteria for Adverse Events (CTC-AE) Dysphagia scores

### Inclusion criteria

Minimum age 18Willing to provide informed consentEastern Cooperative Oncology Group (ECOG) performance status 0–2Histologically confirmed squamous cell carcinomaHPV+ tumor, as determined by: positive p16 status, real-time polymerase chain reaction (PCR) or in-situ hybridization. Central confirmation is not required.Primary tumor site in the oropharynx (includes tonsil, base of tongue, soft palate, walls of oropharynx)Eligible for curative intent treatment, with likely negative resection margins at surgery. For patients where adequate transoral access is in question, they will first have an examination under anesthesia ensure adequate exposure can be obtained prior to randomization.Smokers and non-smokers are included. Patients will be stratified by < 10 versus ≥10 pack-year smoking history. Pack-years are calculated by multiplying the number of years smoked by the number of packs of cigarettes smoked per day. One pack is considered to contain 20 cigarettes.Tumor stage (AJCC 8th edition): T1 or T2Nodal stage (AJCC 8th edition): N0, N1 or N2For patients who may require chemotherapy (i.e. patients with multiple lymph nodes positive or a single node more than 3 cm in size, in any plane; see section 6): complete blood count/differential obtained within 4 weeks prior to randomization, with adequate bone marrow function, hepatic, and renal function, defined as: Absolute neutrophil count > 1.5 × 10^9^/L; Hemoglobin > 80 g/L; platelets > 100 × 10^9^/L; Bilirubin < 35 μmol/L; AST, ALT < 3 x the upper limit of normal; serum creatinine < 130 μmol/L or creatinine clearance ≥50 mL/minHead and neck multidisciplinary clinic (radiation oncologist and surgeon) and multidisciplinary tumor board presentation prior to randomization.

### Exclusion criteria

Unambiguous clinical or radiological evidence of ENE on pre-treatment imaging. This includes the presence of matted nodes, defined as 3 or more nodes that are abutting with loss of intervening fat planes.Serious medical comorbidities or other contraindications to RT, surgery or chemotherapyInability to attend full course of RT or follow-up visitsHistory of previous head and neck RT or previous head and neck cancer within 5 yearsMetastatic disease presentPrior invasive malignant disease within 5 years, with the exception of non-melanoma skin cancerLactating or pregnant women

### Pre-treatment evaluation

The following evaluations are required:
History and physical examination (including laryngopharyngoscopy) by a radiation oncologist and head and neck surgeon within 8 weeks prior to randomizationFor patients where adequate transoral access is in question, they will have an examination under anesthesia to ensure adequate exposure can be obtained prior to randomizationStaging imaging within 12 weeks prior to randomization: Contrast-enhanced CT of the neck and chest or MRI of the neck with CT of the chest or whole body PET/CTDocumentation of smoking historyHistological confirmation of squamous cell carcinomap16+ or HPV+ tumor status, as defined aboveDental evaluation within 6 weeks prior to randomizationAudiogram before initiation of treatment, with baseline CTCAE grade assessmentAssessment of all baseline symptoms, including assessment of dysphagia, using CTC-AE version 4 within 2 weeks prior to randomization. Baseline dysphagia CTC-AE will be scored in all patients.Completion of QOL scoring within 2 weeks of randomizationCBC/differential, hepatic (AST, ALT, total bilirubin) and renal function testing (BUN and creatinine, or creatinine clearance) within 4 weeks prior to randomization, if chemotherapy would be requiredPregnancy test for women of child-bearing age, within 2 weeks prior to randomizationBlood sample for whole genome sequencing analysis prior to initiation of treatmentInformed consents must be obtained prior to any study specific activities

### Interventions

Initiation of treatment should occur within 4 weeks of randomization.

#### Primary radiotherapy (Arm 1)

Treatment in this arm is generally based on Arm 1 of NRG-HN002 [15], and may consist of either radiotherapy alone or concurrent chemoradiation depending on the patient’s clinical nodal status (see Table 1).

**Table 1 Tab1:** Delivery of radiation ± chemotherapy depending on clinical nodal status in Arm 1 (Primary RT)

	Radiation Alone: Accelerated radiation	Concurrent chemotherapy: Weekly cisplatin 40 mg/m^2^ for 6 cycles
Nodal status	Node negative (N0) OR Single node less than 3 cm in maximal diameter	Multiple lymph nodes OR Single lymph node more than 3 cm in maximal diameter
Fractionation	Radiation over 5 weeks, with 6 fractions a week 6th weekly fraction given on a weekday with a minimum 6 h intrafraction interval, or on a Saturday	Daily radiation, Monday-Friday over 6 weeks
Special conditions	In patients > 70 years of age, standard fractionation (daily, Monday-Friday over 6 weeks) can be used at the discretion of the radiation oncologist	In patients who are deemed unfit for weekly cisplatin, the dose and/or schedule can be modified, or cetuximab or weekly carboplatin AUC 1.5 can be used, at the discretion of the medical oncologist.

Dose levels are as follows:
60 Gy in 30 fractions: Gross Tumor and Involved Nodes54 Gy in 30 fractions: High risk subclinical areas.48 Gy in 30 fractions: Low-risk nodal areas

Specific radiotherapy volume definitions for Arm 1 are described in Table 2. In all cases a 5 mm CTV to PTV expansion is to be used.

**Table 2 Tab2:** Specific RT volume definition volumes for Arm 1 (Primary RT)

Radiotherapy Volume	Definition
GTV_P	Gross tumour volume
GTV_N	Gross nodes: – > 1.5 cm long axis – > 1 cm short axis – Necrotic – PET positive
CTV60	Combination of GTV_P and GTV_N with a 5 mm expansion, excluding natural boundaries of spread
CTV54	– A 1 cm expansion on the GTV_P – Any nodal level that contains a positive node. – Any node < 1 cm in short axis the radiation oncologist deems suspicious for harbouring disease. This node plus an additional 5 mm margin will be included in the CTV54. – The first echelon draining nodal levels. This is nearly always level 2, but should include the lateral retropharyngeal nodes (RP) for soft palate and posterior pharyngeal wall extension.
CTV48	– Patients that are node negative: ◦ Ipsilateral: II-IV. RP only if extension to posterior pharyngeal wall or soft palate ◦ Contralateral^a^: II-IV, RP only if extension to posterior pharyngeal wall or soft palate – All patients with N1 (ipsilateral) nodal disease: ◦ Ipsilateral: Ib, II-V, RP ◦ Contralateral^a^: II-IV, RP only if extension to posterior pharyngeal wall or soft palate – All patients with N2 disease: ◦ Ipsilateral and contralateral: Ib, II-V, RP

^a^If treating the contralateral neck

Treatment breaks, early RT termination and discontinuation of systemic therapy is at the discretion of the treating oncologist based on patient treatment toxicity.

##### Salvage surgery

Treatment response will be evaluated 10–12 weeks after completion of RT. This can be done using a CT scan and/or a PET-CT scan.

Treatment of residual disease at the site of the primary tumor will be determined by the treating physicians, and should include surgical salvage if feasible.

Management of residual enlarged lymph nodes in the neck should be guided by standard institutional practice. In general, for patients with residual enlarged nodes on CT, a PET-CT is preferred to confirm fluorodeoxyglucose (FDG) avidity prior to neck dissection. If the PET-CT is negative in the setting of enlarged nodes on CT, then close interval follow-up with repeat CT every 2–3 months is recommended until the lymph nodes resolve. If PET-CT is unavailable, any nodes > 1 cm in short axis should, at a minimum, be carefully followed with repeat CT every 2–3 months until the lymph nodes resolve, with neck dissection at the discretion of the treating physician.

Salvage surgery for the primary tumor or lymph nodes within 5 months of treatment will be considered part of the initial treatment package and scored as persistent disease, not as recurrence. Surgery beyond 5 months post-treatment will be scored as recurrence if malignancy is evident in the pathology specimen.

#### Primary TOS (Arm 2)

Patients with easily accessible oropharyngeal tumors (determined by the consulting surgeon), will proceed directly to TOS. If adequate transoral access is in question, patients will undergo an examination under anesthesia to ensure adequate exposure can be obtained prior to randomization.

Surgical resection will be carried out with at least 1 cm margins. At the time of surgery circumferential margins will be taken and sent for frozen section. The resection will be revised until negative margins are obtained if feasible. Wounds may be closed by primary closure, local flaps (i.e. buccal or palatal flaps) or allowed to heal by secondary intention at the discretion of the treating surgeons. Free flap and regional flaps are not allowed.

Standard selective neck dissections for the lymph node areas at risk will be performed at the time of transoral resection, or as a staged procedure 2 weeks prior to the primary site resection. At this time the lingual and facial branches of the ipsilateral external carotid artery must be ligated on the side ipsilateral to the primary tumor. Patients with tonsillar, lateral palate and lateral pharyngeal cancers, with < 1 cm of base of tongue or palate extension, will undergo ipsilateral neck dissections only. All other patients will undergo bilateral neck dissections. Selective neck dissections will be limited to levels 2–4, unless levels 1 or 5 are involved.

If there is a positive margin at the time of TOS at the primary site, an attempt to clear the positive margin transorally will be allowed. If a positive or close margin is found on the final pathology from the transoral resection, an attempt to clear the margin transorally is allowed within 4 weeks of the original TOS resection. This can be done with or without the robot at the surgeon’s discretion.

A tracheostomy is strongly recommended, but not mandatory, to provide airway protection in the event of swelling and/or bleeding.

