##### Adjuvant radiotherapy

Adjuvant radiotherapy will be determined based on pathological findings. No more than 6 weeks should elapse between the date of surgery and the initiation of adjuvant therapy.

Adjuvant radiotherapy is required for the following risk factors:
ENEPositive margins or close resection margins (< 3 mm)More than 1 lymph node positive, or any lymph node > 3 cm in size on pathologyLVIpT3–4 disease

In situations where PNI alone is present, without the other risk factors above, adjuvant RT is at the discretion of the treating physicians.

Patients with positive margins or ENE will receive a 6-week course of radiation as follows:
60 Gy in 30 fractions: Area of positive margins or ENE54 Gy in 30 fractions: Operative bed, including primary tumor location and all dissected nodal levels48 Gy in 30 fractions: Undissected areas considered to be at low-risk of harbouring microscopic disease.

Patients without positive margins or ENE will receive a 5-week course of radiation as follows:
50 Gy in 25 fractions: Operative bed, including primary tumor location and all dissected nodal levels45 Gy in 25 fractions: Undissected areas considered to be at low-risk of harbouring microscopic disease.

Concurrent chemoradiation will not be delivered in the adjuvant setting unless gross tumor is left behind at the primary site or in the neck AND the patient would have received chemotherapy had they been randomized to Arm 1. Chemotherapy is NOT used for patients with ENE or positive margins. Retrospective surgical data do not support an OS benefit to the use of chemotherapy in HPV+ patients with ENE [19].

Specific radiotherapy volume definitions for Arm 2 are described in Table 3. In all cases a 5 mm CTV to PTV expansion is to be used.

**Table 3 Tab3:** Specific RT volume definition volumes for Arm 2 (Primary TOS) if adjuvant RT is required

Radiotherapy Volume		Definition
With ENE or positive margins (30 fractions over 6 weeks)	Without ENE or positive margins (25 fractions over 5 weeks)	
CTV60		Areas of positive margins and/or ENE
CTV54	CTV50	Entire tumor bed and any dissected neck nodal levels

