CTV48	CTV45	Undissected nodal areas that must be treated based on pathological results. Treatment volumes must include nodal levels adjacent to areas containing involved nodes (eg. if there is a level II node positive, levels Ib and V must be included) – All patients with N1 (ipsilateral) nodal disease: ◦Ipsilateral: Ib, II-V, RP ◦Contralateral^a^: II-IV, RP only if extension to posterior pharyngeal wall or soft palate – All patients with N2 disease: ◦Ipsilateral and contralateral: Ib, II-V, RP

^a^If treating the contralateral neck

The AJCC 8th edition has a pathologically based staging system for HPV+ patients treated with primary surgery that differs significantly from the clinically based staging system used for patients treated with primary radiation. All surgically treated patients will be separately re-staged after the final pathology is available.

In the unlikely event of residual gross disease, the patient should then receive adjuvant treatment using the dose fractionations in Arm 1. In the unlikely scenario where a patient is deemed to have highly aggressive disease (e.g. frank growth/progression during the post-surgical interval), the radiation oncologist may elect to treat with a standard (non-de-escalated) dose of 70 Gy in 35 fractions. Treatment breaks, early RT termination and discontinuation of systemic therapy is at the discretion of the treating oncologist based on patient treatment toxicity.

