### Unilateral vs. Bilateral radiation

Unilateral radiation is recommended if the following criteria are ALL met:
tonsil primary< 1 cm extension into the tongue base or palateno posterior pharyngeal wall extensionno ENEN0, or only a single ipsilateral lymph node positive

Unilateral radiation is optional if the following criteria are ALL met
tonsil primary< 1 cm extension into the tongue base or palateno posterior pharyngeal wall extensionno ENEmore than one ipsilateral lymph node positive, but are all less than 6 cm, and are all in level II.

In all other cases, bilateral radiation is mandatory. These criteria apply to all patients in Arm 1, and to patients in Arm 2 who require adjuvant RT. For the patients in Arm 2 who receive adjuvant RT, these criteria are based on the pathological findings and intraoperative findings, not the pre-operative clinical findings.

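### The Arm 2 neck-dissection rule has no nodal-side criterion, so read literally it gives one-sided dissection to an eligible patient with a lateralised primary and involved contralateral nodes

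*Protocol article*

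**What the plan says.** All of this is in the protocol article.

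- **Eligibility.** Inclusion criteria admit clinical N0, N1 or N2. The nodal exclusion is "Unambiguous clinical or radiological evidence of ENE on pre-treatment imaging", which includes matted nodes. Contralateral nodes are not listed.
- **Surgery.** Primary TOS (Arm 2) opens its neck paragraph with "Standard selective neck dissections for the lymph node areas at risk will be performed at the time of transoral resection" (or staged beforehand). It then names tonsillar, lateral palate and lateral pharyngeal primaries with less than 1 cm of tongue base or palate extension. These patients "will undergo ipsilateral neck dissections only. All other patients will undergo bilateral neck dissections". The one nodal exception, "unless levels 1 or 5 are involved", concerns levels and not side.
- **Radiotherapy volumes.** Tables 2 and 3 carry the row label "All patients with N1 (ipsilateral) nodal disease". For N2 they list "Ipsilateral and contralateral: Ib, II-V, RP", without the footnote that makes contralateral treatment conditional for N1.
- **Radiotherapy side.** Unilateral vs. Bilateral radiation allows one-sided fields only for N0 or ipsilateral nodes, among other conditions. It then says "In all other cases, bilateral radiation is mandatory". In Arm 2 these criteria use pathological and intraoperative findings, not pre-operative clinical ones.
- **Residual disease.** Adjuvant radiotherapy describes undissected treated areas as low risk for microscopic disease. It calls residual gross disease unlikely and sends it to Arm 1 fractionation. Adjuvant chemotherapy is withheld "unless gross tumor is left behind at the primary site or in the neck" and the patient would also have had chemotherapy in Arm 1.

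**The concern.** The two surgical groups cover every Arm 2 patient, and neither mentions which side the nodes are on. The radiotherapy rules start from a similar primary-site test but add a nodal one. An eligible patient whose contralateral neck is clinically involved can therefore meet the surgical criteria for one-sided dissection and fail the radiotherapy criteria for one-sided fields.

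Two things are at stake. If sites follow the sentence as written, known nodal disease is left unoperated in a patient the trial chose to enrol. If sites follow the more general opening phrase, or their own judgement, Arm 2 surgery for these patients varies between centres and departs from the written rule.

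**Working it through.** No arithmetic applies. The check is to follow one patient through the rules: tonsil primary, less than 1 cm tongue base or palate extension, no posterior pharyngeal wall extension, no clear ENE, and clinically involved nodes in the contralateral neck.

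1. **Is the patient eligible?** Yes, if this nodal picture falls within N2. The article does not define N2. Table 2, which concerns clinically staged Arm 1 patients, labels N1 as ipsilateral and gives N2 two-sided volumes. Contralateral or bilateral nodes are the natural reading, but this is an inference. Table 3 supports it less well, because its volumes rest on pathological results and the article says pathological staging differs significantly from clinical staging.

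2. **Arm 1.** The nodes are not confined to the ipsilateral side, so neither the recommended nor the optional unilateral category is met. Bilateral radiation is mandatory, and Table 2 covers both necks.

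3. **Arm 2, surgery.** Site and extension place the patient in the first group: ipsilateral dissection only. The levels exception does not alter the side. The opening phrase about areas at risk points the other way, but it is general and is followed by a specific and exhaustive split.

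4. **Arm 2, adjuvant radiotherapy.** The required indications are all pathological: ENE, positive or close margins, more than one positive node or a node over 3 cm, LVI, or pT3–4. An undissected neck contributes nothing to that list. If pathology shows one ipsilateral node of 3 cm or less and no other listed factor, adjuvant radiotherapy is not required on these criteria. If it is required for LVI alone, the pathological findings for this tonsil primary match the recommended unilateral category. Other findings, such as ENE, would make fields bilateral, but not because of the contralateral nodes. For lateral palate or lateral pharyngeal primaries, bilateral fields follow from site, but only once pathology has called for radiotherapy.

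5. **Arm 2, volumes.** If the contralateral neck is treated as an undissected area, it falls under a description of low microscopic risk. Clinically involved nodes do not fit that description.

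6. **Arm 2, fallback.** The contralateral nodes themselves enter only as residual gross disease, which leads to Arm 1 fractionation. The article calls this unlikely. For this patient, on a literal reading, it follows from the surgical rule.

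Result: the surgical sentence does not fit its own opening phrase, the nodal test for radiotherapy side, the low-risk description of undissected areas, or the description of residual gross disease as unlikely.

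**The case against.** The strongest reply is that the literal reading is not the intended one. The paragraph speaks of areas at risk, and its limit on levels gives way when other levels are involved, so the site rule may have been meant only for an uninvolved contralateral neck. Calling residual gross disease unlikely suggests nobody planned to leave known nodes behind. Every patient also goes to a multidisciplinary clinic and tumour board before randomization. This makes the harmful reading less likely in practice, but it does not remove the word limiting surgery to one side.

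The article also condenses a longer protocol: its inclusion criteria refer to a section 6 that is not shown. An exception for involved contralateral nodes could sit there, which lowers confidence that the trial itself lacks one.

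A reader might infer more than the article supports:

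- **That the surgical and radiotherapy rules are contradictory orders.** They govern different modalities, and ipsilateral dissection followed by bilateral radiation is possible. The defect is a missing statement of how nodal side enters the surgical rule.
- **That the nodes go untreated, or that trimodality treatment must follow.** The residual-disease route exists. Adjuvant chemotherapy needs both gross residual tumour and an Arm 1 indication (multiple nodes, or a single node over 3 cm).
- **That the different site lists are an error.** One-sided surgery is allowed for more primary sites than one-sided radiation. Two treatment strategies may differ in this way, and the radiation list applies equally to both arms.
- **That Arm 2 OS or PFS is biased.** Assuming 5–15% of the 70 Arm 2 patients are N2 and half have lateralised primaries gives 70 × 0.05 × 0.5 = 1.75 to 70 × 0.15 × 0.5 = 5.25 patients. An exact one-sided test against 84% with 70 patients tolerates at most 5 deaths. But neither share is in the article, affected patients are not deaths, and nothing given links the rule to excess mortality.

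**Conclusion.** The point holds as a defect in a stated rule. The surgical section fixes the side of dissection without reference to nodal side, and for one eligible type of patient the result does not fit the rest of the article. The patient needs a lateralised primary, less than 1 cm extension and clinically involved contralateral nodes.

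The conclusion rests on a literal reading of the surgical sentence, on the inference that N2 includes contralateral or bilateral nodes, and on the full protocol not holding an exception. The subgroup is probably small, but its size cannot be derived from the article. The matter is one of patient safety and uniform treatment within Arm 2. No effect on the primary or secondary endpoints is established.

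**What to change.** Reconcile the neck paragraph of Primary TOS (Arm 2) with Inclusion criteria, Tables 2 and 3, Adjuvant radiotherapy, and Unilateral vs. Bilateral radiation. State in the surgical section how a clinically involved contralateral neck is handled when the primary is lateralised. Say what N2 means for this purpose, and make clear whether the residual-disease route is meant to apply to these patients. Which clinical rule to adopt is for the investigators.

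Check the full protocol first. If it already covers the case, a clarification of the article is enough. Otherwise the cost is one wording amendment and a notice to sites, with no change to the sample size or the analysis.
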